### Primary Outcome

We consider the IRD as the primary outcome of DRA treatment (7). The same ultrasonic doctor will measure and evaluate before and after the treatment and after a 6-month follow-up.

### Secondary Outcomes

LA tension evaluation: IRD, continuous midpoint of umbilical cord and knife-edge, level of the umbilical cord, can be measured by ultrasound. Elastography images can be graded using a modified five-point method (17). The scoring criteria were as follows:1 point indicated that most of the lesions or lesions were green; 2 points are red and green areas with <20%; 3 points means the red area is >20% but <50%; 4 points are areas with or without green that are more than 50% red but <80% or more than 80%. Measurements and assessments were made before and after treatment and after 6 months of follow-up.SF-36: It includes physical function, physical pain, general health status, energy, social function, emotional function, mental health, and indicators of health changes in the past year (18). It can reflect a comprehensive summary of the quality of life of the respondents. The higher the score, the healthier you are. Cronbach's α coefficient was 0.838, and Spearman-Brown coefficient was 0.828, indicating good reliability and validity. Measurement and evaluation will be performed before and after the 6-month follow-up.SF-MPQ-2: This is a systemic pain assessment for patients with low back pain. The following quantitative/semi-quantitative data can be obtained from this scale: (1) PRI: The total score of all selected words. (2) NCW: VAS evaluation in the chart. (3) PPI: 6-degree NRS was used to evaluate the total pain intensity. Cronbach's α coefficient is more significant than 0.8, indicating reasonable confidence and validity. Measurements and assessments were made before treatment and after 6 months of follow-up.BMI: The index is used to assess whether a person is thin or overweight. The ratio of being too small (<18.5 for Asian adults) or too large (≥24 for Asian adults) represents an increased incidence of certain diseases and reflects human health status. Measurements and assessments were made before and after treatment and after six months of follow-up.WHR: It is an essential indicator of central obesity and female attractiveness. Measurements and assessments were made before and after treatment and after 6 months of follow-up.

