## Abstract

**Background:** Diastasis rectus abdominis (DRA) is one of the common complications during pregnancy and post-partum, which has psychological and physical effects on post-partum women. Acupuncture, a worldwide alternative therapy, has attracted wide attention in preventing and treating diseases related to pregnancy and childbirth. This study aims to evaluate the efficacy of acupuncture combined with physical training in treating post-partum rectus muscle dissociation.

**Methods:** This is a randomized, controlled trial of DRA in post-partum conducted at Hangzhou Hospital of Traditional Chinese Medicine Affiliated with Zhejiang University of Chinese Medicine. The primary purpose is to evaluate the effectiveness of acupuncture and physical training on DRA in post-partum women. The study will be conducted from March 2022 to March 2023. The acupuncture group received acupuncture and physical training (*n* = 48), the sham acupuncture group received sham acupuncture and physical training (*n* = 48), and the physical training group received physical training (*n* = 48). These experiments perform once/day, five times a week for 2 weeks, followed up for half a year after the end of the course of treatment. Our tests perform a course of treatment, which includes a total of 10 consecutive treatments. Furthermore, the patient will be followed up for half a year after the treatment. Primary and secondary indicators, including inter recti distance (IRD), linea alba (LA) tension, the MOS item short-form health survey (SF-36), short-form McGill pain questionnaire-2 (SF-MPQ-2), body mass index (BMI), waist-to-hip ratio (WHR), leeds dyspepsia questionnaire (LDQ), menstrual distress questionnaire (MDQ), 10 items of edinburgh post-natal depression scale (EPDS-10), the modified body self-image scale (MBIS), international consultation incontinence questionnaire short-form (ICIQ-SF) and hernia-related quality-of-life survey (HerQles), which will be evaluated before and after treatment and half a year after treatment. Adverse events and side effects during each treatment will be collected and recorded.

**Discussion:** There is evidence that acupuncture and physical training can treat DRA in post-partum. In this study, we evaluate the effectiveness of acupuncture in post-partum with DRA.

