### Data Analysis

Based on Preliminary experiment results, we estimated that each of the three clinical researchers involved in the trial would recruit around 28 patients in 3 months. In order to retain most of the patients during follow-up, we gather the patients into a WeChat chatting group to answer their questions anytime. Moreover, actively cooperate with their appointment time. We expect the loss to follow-up to be below 10%.

Baseline characteristics and clinical outcomes are described based on the intention-to-treat population (*n* = 144). Continuous variables are presented as mean (SD), and categorical variables are described as number and percentage.

The principal analysis for primary and secondary outcomes will be a generalized linear model (GLM) including the intervention arm, the dependent variable's baseline score, and other variables imbalanced at baseline as covariates. The dependent variable will be the post-intervention score. The GLM does not need a normal distribution in the dependent variable. However, the distribution of the variables will be analyzed using de Shapiro- Wilk test to perform an adequate descriptive analysis. The choice of the link function will depend on the distribution of the variable.

Other variables will be added as confounders in the model as secondary sensitivity analyses. We will first fit separate models, including each confounder, one at a time. Those variables whose inclusion in the model changes the estimates' treatment effectiveness by at least 10% will be considered as confounders. As suggested in the CONSORT statement, decisions about confounders will not be based on *P*-value.

Missing data of withdrawn participants will be accommodated with multiple imputation procedures in Stata 25.0 software (Stata Corporation). All *P*-values were from 2-sided tests, and results were deemed statistically significant at *P* < 0.05.

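### The five-point linea alba scale defines only four grades, SF-36 and SF-MPQ-2 visits differ between Abstract and body, and HerQles is in no outcome section

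*Protocol article*

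**What the plan says.** **LA tension.** Secondary Outcomes of the protocol article states: "Elastography images can be graded using a modified five-point method". It then defines 1, 2, 3 and 4 points and stops. The first grade has no percentage: "1 point indicated that most of the lesions or lesions were green". Grade 2 is below 20%, with red implied as the colour, and grade 3 is above 20% and below 50% red. The last grade reads: "4 points are areas with or without green that are more than 50% red but <80% or more than 80" per cent.

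**Visits.** After listing all 12 instruments, the Abstract says of them: "which will be evaluated before and after treatment and half a year after treatment". Secondary Outcomes says of SF-36: "Measurement and evaluation will be performed before and after the 6-month follow-up". Of SF-MPQ-2 it says: "Measurements and assessments were made before treatment and after 6 months of follow-up". LA tension, BMI, WHR and all five instruments under Other Observation Items get three assessments in the body, as does the primary outcome, inter recti distance (IRD).

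**HerQles.** It is in the Abstract list and the Abbreviations, but not in Primary Outcome, Secondary Outcomes or Other Observation Items.

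**Analysis.** Data Analysis plans one generalized linear model for primary and secondary outcomes, adjusted for the baseline score of the outcome. It adds: "The dependent variable will be the post-intervention score". It does not name the visit, and it leaves the link function to the distribution of the variable.

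**The concern.** These are stated rules and schedules that disagree with each other. They are not details that a short article leaves to a fuller document.

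A grader who follows the LA text cannot award 5 points and must give one score to everything from just over half red upwards. LA tension is the first secondary outcome listed, so its scoring rule should be fixed before images are read.

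A site that follows the body text on visits will not collect SF-MPQ-2 at the end of treatment. A pain score not taken at that visit cannot be recovered later. For SF-36 the staff must guess which of two visits is meant.

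For HerQles, the reader cannot tell whether it is a secondary outcome, and so covered by the planned model, or a further observation item. If this stays open, the LA grading rule, the visit used for pain and quality of life, and the standing of HerQles could all be settled after data have been seen.

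**Working it through.** The plan gives no figure to reproduce on this point. The check is a count and a side-by-side reading.

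**1. LA grades, as Secondary Outcomes defines them**

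| Image | Score |
|---|---|
| mostly green, no percentage | 1 |
| below 20% (red implied) | 2 |
| exactly 20% red | none |
| above 20%, below 50% red | 3 |
| exactly 50% red | none |
| above 50%, below 80% red | 4 |
| above 80% red | 4 |
| no definition given | 5 |

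- Grades named 5, grades defined 4: 5 − 4 = 1 missing.
- Width of the bands in percentage points of red area: grade 2, 20 − 0 = 20; grade 3, 50 − 20 = 30; grade 4, 100 − 50 = 50. The merged grade covers half of the possible range.
- A move between above 80% and 51% red, in either direction, scores 4 − 4 = 0. With the top band split it would score one grade.
- Read literally, exactly 80% is in neither half of grade 4, although both sides of it score 4.
- Grade 1 overlaps grades 2 and 3, because an image with less than half its area red may still be mostly green.

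**2. Assessments per instrument**

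| Instrument | Abstract | Body |
|---|---|---|
| IRD, LA tension, BMI, WHR | 3 | 3 |
| LDQ, MDQ, EPDS-10, MBIS, ICIQ-SF | 3 | 3 |
| SF-MPQ-2 | 3 | 2 (baseline, 6 months) |
| SF-36 | 3 | 2 (ambiguous) |
| HerQles | 3 | 0 (not in an outcome section) |

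The instruments number 4 + 5 + 1 + 1 + 1 = 12. Nine of them agree between Abstract and body, so the three exceptions are not a drafting convention.

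**3. The two readings of the SF-36 sentence**

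- If the earlier occasion is before treatment, SF-36 has baseline and 6 months, and the end-of-treatment value is missing.
- If the earlier occasion is just before the follow-up period, SF-36 has end of treatment and 6 months. The baseline is then missing, and the model in Data Analysis requires it as a covariate.

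Either way, one of the three assessments in the Abstract is lost.

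**The case against.** The best reply is that these are slips of wording in a condensed article. The grade 4 sentence reads like two definitions run together. If grade 5 was lost only in writing, the trial may be using a complete scale taken from the cited source, and no score is affected. Images at exactly 20% or 50% would in any case be rare. For the visits, correcting the Abstract would remove the conflict as well as adding assessments would, and nothing in the document requires pain or quality of life to be measured at the end of treatment. None of this touches the primary outcome.

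Much of that stands, and it rules out several stronger readings:

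- *These outcomes cannot enter the planned model.* This does not follow. Data Analysis names no visit, a 6-month value is also post-intervention, and a four-grade score can be modelled.
- *The merged grade biases LA tension towards no effect.* The article does not say whether more red is better or worse, and it gives no baseline distribution. If few women exceed 80% red, the effect could be nil.
- *HerQles is never scheduled.* The Abstract does schedule it. What is missing is its place in an outcome section.
- *SF-36 certainly lacks an end-of-treatment value.* That is one of two readings.

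What the reply does not remove is the text itself. The article states a scoring rule that cannot produce its own fifth grade, and two schedules that cannot both be followed.

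**Conclusion.** The point holds as a set of internal contradictions in the secondary outcomes. One of five LA grades is undefined and the top two bands share a score. Two of five secondary outcomes have visits that differ between Abstract and body: SF-MPQ-2 plainly lacks the end-of-treatment assessment in the body, and SF-36 lacks either that or the baseline. One of 12 instruments has no outcome tier.

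The loss of sensitivity at the top of the LA scale assumes that images are graded as the article is worded. The loss of the SF-MPQ-2 value assumes that sites follow the body and not the Abstract. The documents give neither the size nor the direction of any effect on estimates. The IRD analysis, the sample size and the error rates do not change. The matter should still be corrected, because a questionnaire that was not given cannot be recovered and the correction is cheap.

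**What to change.** 1. **LA tension.** Split the merged top band into grades 4 and 5, checked against the source cited for the scale. Make the bands exhaustive and non-overlapping: assign each boundary value to one grade, and give grade 1 a limit that separates it from grades 2 and 3. Do this before any images are graded.
2. **SF-36 and SF-MPQ-2.** State baseline, end of treatment and 6 months for both in Secondary Outcomes, in line with the Abstract. Cutting the Abstract back would also remove the conflict, but it would give up a value that cannot be obtained later.
3. **HerQles.** Place it in an outcome section with its visits, or delete it from the Abstract.

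The cost is protocol wording and two questionnaires at an end-of-treatment visit that already exists for the other measures. The only downside is a few minutes of participant time.

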### Other Observation Items

LDQ: The questionnaire is a dimensional-symptom-specific scale tool for assessing disease conditions. The Cronbach's α coefficient of the table is 0.908, and the Cronbach's α coefficient of each dimension is 0.448–0.990, indicating good internal consistency and high measurement reliability (19). Measurements and assessments were made before and after treatment and after 6 months of follow-up.MDQ: To assess the status of the menstrual disease. The overall Cronbach's α coefficient was 0.937 (*P* < 0.001), and the Cronbach's α coefficients of each dimension ranged from 0.652 to 0.862 (20). Measurements and assessments were made before and after treatment and after 6 months of follow-up.EPDS-10: The revised EPDS has a confidence of 0.76, content validity of 0.93, and a recommended critical value of 9.5 points (21). The measurement and evaluation will be taken before and after the treatment and after a 6-month follow-up.MBIS: MBIs have been shown to work via changes in specific aspects of psychopathology, such as cognitive biases, affective dysregulation, and interpersonal effectiveness (22). The measurement and evaluation will be taken before and after the treatment and after a 6-month follow-up.ICIQ-SF: International Association for Urine Control Questionnaire. The Chinese version of Cronbach's α coefficient indicates an internal consistency of 0.72–0.8 (22). After the inspection. Measurements and assessments were made before and after treatment and after 6 months of follow-up.

### Adverse Events Reporting and Safety Monitoring

Safety: Adverse events (AE), side effectiveness (SE) such as falls, joint sprains will be recorded during the evaluation.

Compliance: Incomplete information and number of shedding for the two selected cases were recorded during and after the evaluation.

Acupuncture and exercise training were used as intervention items in this study. Before participating in the study, each subject underwent clinical diagnosis and contraindications, and detailed records were made during the treatment process. DURING THE EXPERIMENT, any AE, SE (fall, joint sprain, bleeding, post-stitch, needle blocking, etc.) will be recorded in detail and reported to the project leader. Subjects with adverse events will be treated in the hospital where the project is being implemented, and the project team will bear the treatment and examination costs.

### Data Analysis

Based on Preliminary experiment results, we estimated that each of the three clinical researchers involved in the trial would recruit around 28 patients in 3 months. In order to retain most of the patients during follow-up, we gather the patients into a WeChat chatting group to answer their questions anytime. Moreover, actively cooperate with their appointment time. We expect the loss to follow-up to be below 10%.

Baseline characteristics and clinical outcomes are described based on the intention-to-treat population (*n* = 144). Continuous variables are presented as mean (SD), and categorical variables are described as number and percentage.

The principal analysis for primary and secondary outcomes will be a generalized linear model (GLM) including the intervention arm, the dependent variable's baseline score, and other variables imbalanced at baseline as covariates. The dependent variable will be the post-intervention score. The GLM does not need a normal distribution in the dependent variable. However, the distribution of the variables will be analyzed using de Shapiro- Wilk test to perform an adequate descriptive analysis. The choice of the link function will depend on the distribution of the variable.

Other variables will be added as confounders in the model as secondary sensitivity analyses. We will first fit separate models, including each confounder, one at a time. Those variables whose inclusion in the model changes the estimates' treatment effectiveness by at least 10% will be considered as confounders. As suggested in the CONSORT statement, decisions about confounders will not be based on *P*-value.

Missing data of withdrawn participants will be accommodated with multiple imputation procedures in Stata 25.0 software (Stata Corporation). All *P*-values were from 2-sided tests, and results were deemed statistically significant at *P* < 0.05.

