## Background

Diastasis recti abdominis is a condition in which both rectus abdominal muscles disintegrate to the sides, accompanied by the extension of the linea alba tissue and bulging of the abdominal wall (1). 30–70% of pregnant women develop DRA during pregnancy (2). Between 35 and 70 percent of pregnant women do not recover after giving birth without treatment or exercise (3). In addition, 39% to 45% of women still have DRA at 6 months post-partum, and the incidence of DRA at 1 year post-partum is 23–32% (1). DRA has both psychological and physical effects on post-partum women. Women with DRA primarily receive the application of support band and abdominal band during pregnancy and post-partum (4), electrical stimulation, surgical repair (5), and physical training (6). There is a lack of unified and effective treatment, and there are few studies on the efficacy and safety of DRA physical training (5, 7). As a worldwide alternative therapy, acupuncture has received wide attention in preventing and treating diseases related to pregnancy and childbirth.

Acupuncture combined with physical training can significantly improve tissue excitability, which improves blood circulation and systolic muscle function (8) and adjust the mechanical balance of the post-partum abdominal muscle group. In abdominal physical training, the increase of abdominal pressure makes the pelvic floor vulnerable to adverse effects and causes or exacerbates pelvic floor dysfunction. Acupuncture can well cause the secondary synergism of pelvic floor muscles by activating the transverse abdomens (9, 10).

However, the long-term efficacy is still unclear, and there is a lack of solid objective evidence. To date, no RCT studies the impact of acupuncture on DRA or evaluates the standardized application of DRA by acupuncture. This study comprehensively evaluates the effectiveness and safety of acupuncture in the treatment of post-partum DRA, the effective, and safety of DRA physical training. It provides a reference for clinical treatment of post-partum DRA.

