### Sample Size

According to previous similar reports (13), the average value of IRD in the physical training group was 2.09 after treatment, and the average value of IRD in the acupuncture and physical training group was expected to be 1.43 after treatment in this study. Three groups were set up in this study. The test level was α = 0.05, the test efficiency was 1–*β* = 0.90, and the two-sided test was conducted. The sample size was estimated by PASS15.0 software (13), effectiveness size is 0.313249. Considering 2-sided *P*-values to be deemed statistically significant at *P* < 0 0.05 and a power of 90%, 43 participants would be required per group (nQuery Advisor, version 4.0; Statistical Solutions). Estimating that 10% of patients might be lost to follow-up, we planned to enroll a total of 144 participants, with 48 in each group.

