### Participants and Recruitment

The study was conducted from March 2022 to March 2023. The acupuncture group received acupuncture and physical training (*n* = 48), the sham acupuncture group received sham acupuncture and physical training (*n* = 48), and the physical training group received physical training (*n* = 48).

Participants were recruited from inclusion criteria:

(1) A female aged 18–45 years with no previous history of pathological rectus abdominal dissection;(2) Vaginal delivery, 42 days to 1 year post-partum;(3) DRA diagnostic criteria:The patient should keep in the supine position, with knees bending about 90°, the whole body relaxed, and the soles of the feet flat. The examiner shall put the abdomen of one hand finger on the umbilical level of the patient;The patient is told to breathe through the abdomen and to lift one's head and shoulders slightly off the bed;

Measuring the width of the finger inserted by the examiner, DRA is diagnosed when IRD ≥ 2 cm (14–16).

(4) No cognitive barriers, able to understand and communicate correctly;(5) Have not received treatment for DRA in other hospitals or institutions;(6) Those who sign the informed consent cooperate with the treatment and can adhere to the completion of all treatment as planned.

Patients who meet the above six criteria can be included in this study.

The subjects studied for DRA in post-partum women should follow the following exclusion criteria:

(1) One is suspected or diagnosed with severe spinal lesions (such as spinal fractures, metastases, inflammatory or infectious diseases, cauda equina syndrome/widespread neurological disease) and neurological injury;(2) One has motor contraindications or severe infectious diseases such as fractures, severe heart disease, hypertension, cancer;(3) Any plans for surgery soon;(4) History of cesarean section;(5) Abdominal operation history;(6) Any of the above shall be excluded.

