### Randomization and Binding

A total of 144 eligible patients were recruited and randomly assigned at a 1:1:1 ratio to receive acupuncture treatment or sham acupuncture treatment or be placed on a physical training. Central randomization, using an online or messaging system, was performed by the Brightech Magnsoft Data Services. The randomization sequence was generated in blocks of varying sizes and stratified by centers.

The acupuncture and sham acupuncture groups were blinded, while those in the physical training group were not. All clinical examinations were performed by [name] and [name] physiotherapists blinded to data collected through the questionnaire. Due to iodophor disinfection traces in the abdomen after electroacupuncture, the therapists knew the groups, so [name] performed electroacupuncture treatment after rehabilitation exercise first. All the therapists did not know the purpose of the experiment.

The acupuncture and sham acupuncture groups were blinded, while those in the physical training group were not. All clinical examinations were performed by [name] and [name], two physiotherapists blinded to data collected. Due to iodophor disinfection traces in the abdomen after electroacupuncture, the therapists knew the groups. So [name] performed electroacupuncture treatment after rehabilitation exercise first. Outcome assessors, data collectors, and statisticians did not know the purpose of the experiment and were blinded to the treatment allocation.

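### The principal model for IRD is not fixed before data are seen: covariates depend on observed imbalance, the link on the observed distribution, and time since delivery enters only by chance

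*Protocol article*

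**What the plan says.** All references are to the protocol article.

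- **Data Analysis, principal model.** One generalized linear model serves the primary and secondary outcomes. It contains arm, the baseline value of the outcome "and other variables imbalanced at baseline as covariates". No variables are listed and no threshold for imbalance is given.
- **Data Analysis, link.** "The choice of the link function will depend on the distribution of the variable".
- **Data Analysis, confounders.** Further variables are tried one at a time, and those that change the estimated "treatment effectiveness by at least 10% will be considered as confounders". The section labels this step a secondary sensitivity analysis and says that P-values will not decide it.
- **Participants and Recruitment.** Entry window: "Vaginal delivery, 42 days to 1 year post-partum".
- **Background.** "39% to 45% of women still have DRA at 6 months post-partum"; the figure for 1 year is 23-32%.
- **Randomization and Binding.** "The randomization sequence was generated in blocks of varying sizes and stratified by centers". Study Design and Setting names one hospital.

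**The concern.** In a randomised trial, baseline imbalance arises by chance. The case for adjusting for a variable is that it predicts the outcome, not that it differs between arms in this sample. If imbalance is the entry rule and is left undefined, whoever analyses the data decides which model is primary.

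The link raises a second problem. For IRD, an identity link estimates a difference in means and a log link a ratio of means. If the link waits for the observed distribution, the scale of the primary result is open until outcomes are in hand.

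The third problem is what the rule leaves out. Women enter from 6 weeks to 1 year after delivery, and the Background figures show diastasis becoming less common over that period. Time since delivery is neither a fixed covariate nor a stratification factor. At stake are the credibility of the primary estimate and some precision.

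**Working it through.** **1. The plan's own figure, for context.** Inputs from Sample Size: "The test level was α = 0.05", "the two-sided test was conducted", power 90%, three groups, effect size 0.313249, 43 per group, 10% loss. Reading the effect size as Cohen's f (an assumption; the metric is not named), the noncentrality is N·f² = 129 × 0.313249² = 12.66 on 2 and 126 degrees of freedom. Power is 89.3%, close to the stated 90%. Then 43/0.90 = 47.8, so 48 per group and 144 in total. The figure reproduces closely.

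**2. How much the undefined imbalance rule leaves open.** Assume five independent candidate covariates and 43 per arm in three arms. The chance that at least one counts as imbalanced is:

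| Criterion | Chance of at least one |
|---|---|
| P < 0.05 | 1 − 0.95⁵ = 23% |
| largest pairwise standardised difference > 0.5 | 27% |
| largest pairwise standardised difference > 0.2 | 99% |

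The threshold that the plan does not state largely decides whether the primary model has extra covariates.

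**3. Type I error.** Defining imbalance as P < 0.05 (an assumption), simulated error under selection is 4.0-4.8% with two arms of 48 and 4.5-4.8% with three arms of 43. If the smaller P-value of the selected and unselected models were reported, it would be 5.2-5.5%. Imbalance selection alone does not inflate the error rate. Choice of link was not simulated.

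**4. Precision from time since delivery.** Under a P < 0.05 rule, a variable with no true difference enters in about 5% of trials, so power stays near that of the model with baseline only.

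Assumptions: two-arm contrast, 48 per arm, effect d = 0.5 SD, correlation of baseline with final IRD 0.5, and correlation r of time with final IRD 0.3 or 0.5. The noncentrality is d/√(residual variance) × √(48/2), referred to a t distribution with 93 degrees of freedom (baseline only) or 92 (time added).

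- Baseline only: residual 1 − 0.25 = 0.75.
- Time equally correlated (r) with baseline and final IRD: R² = (0.25 + r² − 2·0.5·r·r)/(1 − r²) = 0.25/(1 − r²).
- Time independent of baseline IRD: residual 0.75 − r².

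| Model | r | Residual variance | Noncentrality | Power |
|---|---|---|---|---|
| Baseline only | – | 0.750 | 2.83 | 79.9% |
| Plus time, equal correlation | 0.3 | 0.725 | 2.88 | 81.2% |
| Plus time, equal correlation | 0.5 | 0.667 | 3.00 | 84.3% |
| Plus time, independent of baseline | 0.3 | 0.660 | 3.02 | 84.7% |
| Plus time, independent of baseline | 0.5 | 0.500 | 3.46 | 92.9% |

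The gain is about 1-4 points in the first case and 5-13 in the second.

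**5. The 10% rule, as a sensitivity step.** With three arms of 43 and no treatment effect, the rule flags a pure-noise covariate in 33% of trials (39% with two arms of 48). It flags one that explains 10-30% of residual variance in 80-90%. At a standardised difference of 0.66 (Cohen's f as above, sham equal to training), the latter falls to 33-58%. The rule is unstable when the estimate is near zero, because any small shift is then a large percentage.

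**The case against.** **The 10% rule.** A reader might infer that it selects covariates for the principal model. It does not: Data Analysis confines it to secondary sensitivity analyses, so it leaves the primary estimate and P-value untouched. Nor does the plan permit reporting whichever fitted model is significant; it names one principal analysis.

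**Error rate.** A reader might infer that imbalance selection inflates type I error. The simulations show the opposite, slightly.

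**Time since delivery.** Calling it the main prognostic factor goes beyond the documents. The Background figures describe post-partum women in general, whereas participants must have an IRD of at least 2 cm at entry, so late entrants are women whose separation has not resolved. Baseline IRD is already in the model and no figure ranks the two. If separation resolves with time, time should correlate with baseline IRD, which makes the smaller gain (1-4 points) the more plausible one. With a 0.66 SD contrast instead of 0.5, baseline-adjusted power is already about 96%, and adding time gives 97-98%. All of this stands and limits the size of the point.

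**Link.** The same model must serve an ordinal elastography grade and several questionnaire scores, where matching the link to the type of variable is sensible. That is fair for the secondary outcomes, but it is no reason to leave the scale open for IRD.

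**Left to the SAP.** A separate plan might name covariates and link. But the article does more than stay silent: it states data-dependent rules, and an SAP could fix the model only by overriding them.

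**Conclusion.** The point holds in this limited form. As written, neither the covariates nor the effect scale of the primary IRD analysis is fixed before data are seen, and a plausibly prognostic variable known at entry is used only if chance makes it imbalanced. The consequences are analyst discretion and a modest loss of precision. Under the stated assumptions (0.5 SD effect, baseline correlation 0.5, 48 per arm, r of 0.3-0.5), fixing time since delivery in the model moves power from about 80% to 81-84%, or to 85-93% if it is unrelated to baseline IRD. The documents supply none of these correlations. The change should be made because it removes discretion at almost no cost; the power gain is secondary.

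The stratification statement is a separate and harmless inconsistency: with one hospital, stratifying by center balances nothing.

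**What to change.** Before unblinding:

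1. For IRD, specify a Gaussian model with identity link and arm, baseline IRD and weeks since delivery (continuous) as covariates, regardless of observed balance.
2. Delete the imbalance rule from the principal analysis.
3. Keep covariate-adjusted sensitivity analyses secondary, with a set named in advance (for example age and BMI) in place of the 10% change rule.
4. Strike or correct the statement on stratification by center.

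Cost: wording, and about one degree of freedom in the primary model. Time since delivery is needed to check eligibility, so no new data are required.
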